### Outcome measures

All patients enrolled in this trial will be followed up regularly at stated intervals after the surgery for an average of 5 years. During the follow-up visits, patients will undergo endoscopy, laboratory tests, and radiography if necessary as described in Table 1.

**Table 1 Tab1:** Summary of the follow-up visit schedule and assessed parameters at each time point

	Preoperative	3 M	6 M	9 M	12 M	18 M	24 M	36 M	48 M	60 M
Endoscopy	*	**	*		*		*	*	*	*
Laboratory	*	*	*		*		*	*	*	*
CT scan	*	*	*		*		*	*	*	*
Upper digestive tract radiography	**	*	*		*		*	*	*	*

*Evaluation at the designated time point, **evaluation if necessary

The primary assessment indices of the study are reflux gastritis, esophagitis, bile regurgitation, and anastomotic ulcer. Endoscopy will be used to help with standardized assessment of these indices during the follow-up visits. Full details for the Los Angeles classification of the severity of reflux esophagitis are shown in Table 2.

**Table 2 Tab2:** Los Angeles classification of the severity of reflux esophagitis

Grade	Manifestation
A	One (or more) mucosal break(s) no longer than 5 mm that does not extend between the tops of two mucosal folds
B	One (or more) mucosal break(s) more than 5 mm long that does not extend between the tops of two mucosal folds
C	One (or more) mucosal break(s) that is continuous between the tops of two or more mucosal folds but which involve(s) less than 75% of the circumference
D	One (or more) mucosal break(s) that involve(s) at least 75% of the esophageal circumference

The secondary assessment indices are nutritional status, quality of life, perioperative complications, overall survival rate, and others. Nutritional status includes body mass index (BMI), hemoglobin, albumin, total protein, pre-albumin, transferring, and other indices such as appetite and Onodera’s prognosis nutritional index (PNI). Quality of life will be assessed by the gastrointestinal symptom rating scale (GSRS) and Visick score (shown in Additional file 1: Tables S1 and S2). Perioperative complications occurring within 30 days after the surgery include anastomotic fistula and anastomotic stenosis. Overall survival rates for 1, 3, and 5 years after the surgery as well as recurrence and metastasis rates will be calculated. Other indices include surgery time, intraoperative blood loss, length of hospital stay, and hospital cost.

All the results of the outcome measures will be recorded at the data center. Only follow-up data of patients without recurrence after 1 year of surgery will be analyzed at the end of the study.

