### Sample size

Our study is designed as a superiority trial whose primary outcome is postoperative reflux gastritis or not. Current experience suggests the predicted rate of postoperative reflux gastritis will be 8% for the uncut Roux-en-Y anastomosis group and 12% for the control group of Billroth II anastomosis. The difference test was used to estimate the sample size with 80% test power and a 5% significance level. Accounting for a 15% drop-out rate and the 1:1 allocation ratio, the total number of patients required per group is 416 (832 in total), which was calculated using the software PASS version 11.0. Considering a completion rate of 75% for each coordinating center, 1040 envelopes were designed for random allocation. The number of cases will be increased if necessary according to the results of the interim analysis.

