#### Statistical analysis

Statistical analysis planning was formulated by health statisticians as well as key researchers. We will use SPSS or SAS to analyze the data. For survival analyses, Kaplan-Meier curves and log rank tests will be used. The Cox proportional hazards model will be used for prognosis analysis. Categorical variables will be analyzed by Pearson’s χ^2^ test or Fisher’s exact test, and continuous variables will be evaluated by Student’s *t*-test or an appropriate non-parametric method as required. The level of statistical significance will be set at 5%.

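### No use is stated for the preoperative endoscopy when the arms are compared on oesophagitis and bile regurgitation, although patients with either condition before surgery are eligible

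*Protocol article*

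**What the plan says.** Four points in the protocol article bear on this.

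- **Outcome.** Outcome measures: "The primary assessment indices of the study are reflux gastritis, esophagitis, bile regurgitation, and anastomotic ulcer". Table 2 prints Los Angeles grades A to D for oesophagitis. The text does not say whether the outcome is any, new or worsened oesophagitis.
- **Eligibility.** The only oesophageal condition named under Exclusion criteria is malignancy. Reflux oesophagitis and bile reflux are not listed. A general clause lets researchers exclude unsuitable patients, but it names neither condition.
- **Timing.** Table 1 marks the preoperative endoscopy as due for all patients, not only when necessary. On its purpose the section says: "Endoscopy will be used to help with standardized assessment of these indices during the follow-up visits". Elimination criteria lists six time-points for evaluating the primary outcome, from 6 months to 5 years, all after surgery.
- **Analysis.** Statistical analysis: "Categorical variables will be analyzed by Pearson’s χ^2^ test or Fisher’s exact test". No baseline term or stratification appears. The two planned subgroup factors are NRS2002 score and pathological stage, so endoscopic status before surgery is not among them.

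The Sample size section is narrower: "Our study is designed as a superiority trial whose primary outcome is postoperative reflux gastritis or not". Its planning rates are "8% for the uncut Roux-en-Y anastomosis group and 12% for the control group of Billroth II anastomosis". No rate is given for oesophagitis or bile regurgitation.

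**The concern.** Oesophagitis and bile regurgitation can be present before the operation, whereas an anastomotic ulcer cannot. A patient who enters with oesophagitis and still has it at 6 months is positive at follow-up whichever reconstruction was done. Such patients add events that say little about the anastomosis. If they are equally frequent in both arms, the absolute difference shrinks while the event rate, and with it the variance, rises. Any chance imbalance in preoperative disease also passes into the result. The trial already schedules the examination that would identify these patients, so leaving it out of the comparison gives up precision that costs almost nothing to keep.

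**Working it through.** **Inputs from the protocol.** 8% and 12% (reflux gastritis, Sample size section); 416 per group; 15% drop-out; 5% significance level. Evaluable per arm: 416 × 0.85 = 353.6, taken as 354.

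**Inputs assumed.** Baseline prevalence b and persistence after surgery, neither of which is in the documents. The 8% and 12% are borrowed as new-onset rates, because no rates are given for the two indices concerned. Tests are taken as two-sided; the protocol does not state sidedness.

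**The plan's own figure.** The standard two-sided calculation gives
n = [1.96 √(2 × 0.10 × 0.90) + 0.842 √(0.12 × 0.88 + 0.08 × 0.92)]² / 0.04² = 882 per arm, or 882 / 0.85 = 1,038 with drop-out. One-sided it is 695, or 818 with drop-out. The stated 416 per group is not reproduced. That is a separate matter; here it only explains why the power figures below start from 43% and not 80%.

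**Equal, full persistence in both arms.** Follow-up rate = b + (1 − b)p, so the difference is (1 − b) × 4 points.
Crude power = Φ(difference / √[(p₁(1 − p₁) + p₂(1 − p₂)) / 354] − 1.96).
In a Cochran-Mantel-Haenszel test stratified by preoperative status, the stratum with prior disease has no variation (everyone is positive). The test therefore rests on 354(1 − b) patients per arm at 8% v 12%.

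| b | Follow-up rates | Difference (points) | Crude power | Stratified power |
|---|---|---|---|---|
| 0% | 8.0% v 12.0% | 4.0 | 43% | 43% |
| 2% | 9.8% v 13.8% | 3.9 | 37% | 42% |
| 5% | 12.6% v 16.4% | 3.8 | 30% | 41% |
| 10% | 17.2% v 20.8% | 3.6 | 23% | 39% |
| 20% | 26.4% v 29.6% | 3.2 | 16% | 35% |

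Worked line, b = 10%: standard error √[(0.172 × 0.828 + 0.208 × 0.792) / 354] = 0.0295; 0.036 / 0.0295 = 1.22; Φ(1.22 − 1.96) = 23%. Stratification does not restore the 4-point contrast across all patients. It removes the noise.

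**Chance imbalance.** At b = 10% the standard error of the between-arm difference in preoperative prevalence is √(2 × 0.1 × 0.9 / 354) = 2.3 points, against a sought difference of 4 points.

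**Unequal persistence.** Let b = 10%, with persistence 100% under Billroth II and 50% under uncut Roux-en-Y.

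- Follow-up rates: 0.1 × 0.5 + 0.9 × 0.08 = 12.2% and 0.1 + 0.9 × 0.12 = 20.8%, a difference of 8.6 points.
- Crude power: Φ(0.086 / 0.0277 − 1.96) = 87%.
- Stratified test: each stratum's difference is weighted by half its per-arm size, giving 17.7 × 0.50 + 159.3 × 0.04 = 15.22. The null standard deviation is √(17.7 × 0.75 × 0.25 + 159.3 × 0.10 × 0.90) = 4.20. The standard deviation under the alternative is √(17.7² × 0.25 / 35.4 + 159.3² × 0.1792 / 318.6) = 4.06. Power = Φ((15.22 − 1.96 × 4.20) / 4.06), about 96%.

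A simulation of both tests agreed to within about half a percentage point (crude 23% and 87%, stratified 39% and 95.5% in the two 10% scenarios).

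**The case against.** The strongest reply is that the article is silent here, not wrong. A condensed protocol may leave event definitions and baseline adjustment to the full protocol or analysis plan, and neither is shown. That stands against several stronger readings:

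- **That the preoperative endoscopy is discarded, or that old disease is declared a postoperative event.** A reader might infer this, but no sentence says either.
- **That a patient who worsens from grade A to grade C counts the same as one who is unchanged.** The documents do not say that the grades are collapsed to yes or no. Only reflux gastritis is worded as binary.
- **That the power figures measure this trial's loss.** They borrow reflux gastritis rates and an assumed prevalence. With no prior disease, or none that persists, there is no loss.
- **That the arm difference must be diluted.** The Background credits uncut Roux-en-Y with an anti-reflux function. If it resolves existing disease more often, follow-up status captures a real benefit and the difference can widen, as the unequal case shows.
- **That the outcome should be redefined as new-onset or worsened disease.** This changes the question and would discard that benefit.

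What the objection does not reach is the stated method. The article does fix the evaluation times, all postoperative, and does name an unadjusted test. Replacing that test with one that uses a finding already scheduled improves power in both 10% scenarios worked above, and costs nothing when there is no baseline disease.

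**Conclusion.** The point holds as an inexpensive improvement to the stated analysis of two of the four primary indices, oesophagitis and bile regurgitation. It does not show bias towards either arm: randomisation balances preoperative disease on average, and follow-up status is a valid comparison. What is at stake is precision, plus a smaller difference if disease persists equally in both arms.

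The size cannot be fixed from the documents. Under the assumptions given (354 evaluable per arm, 8% v 12% new onset, equal and full persistence), crude power ranges from 43% with no prior disease to 16% at 20% prevalence. Stratified power ranges from 43% to 35%. The sample size for reflux gastritis is not directly affected, since that outcome is already worded as postoperative and no rate for the other indices enters it.

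**What to change.** In Outcome measures, require the Los Angeles grade and any bile reflux finding to be recorded at the preoperative endoscopy that Table 1 already schedules.

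In Statistical analysis, replace the unadjusted test for oesophagitis and bile regurgitation with a comparison stratified by or adjusted for preoperative status, for example Cochran-Mantel-Haenszel or logistic regression. The stratified test is the safer default if nearly all patients with prior disease remain positive, since a logistic model can then fail to converge. Report new-onset or worsened disease as a supportive analysis only, so that resolution of prior disease still counts in the main comparison.

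Eligibility, visits and patient numbers stay as they are. The cost is one baseline field on the case report form, where it does not already exist, and slightly more analysis work.

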## Discussion

In recent years, gastric cancer has remained the fourth most common malignant disease worldwide, and lower one-third gastric cancer is the most common type [1–3]. Distal gastrectomy with D2 lymph node dissection has been thought to be the standard surgery for these patients [4]. However, reconstruction of distal gastrectomy remains controversial; Billroth II anastomosis has gained widespread popularity for its simplicity and lower risk of anastomotic tension. In addition, Billroth II anastomosis may cause bile reflux gastritis, esophagitis, or dumping syndrome [13]. Therefore, the preferred way to perform reconstruction after distal gastrectomy is still debated. Uncut Roux-en-Y anastomosis is another method of reconstruction with an anti-reflux function as well as the ability to eliminate the occurrence of Roux stasis [20, 21]. However, it requires further investigation to have an impact in clinical practice.

Many investigators have evaluated the anastomosis after distal gastrectomy by randomized controlled trials [19, 26–29]. However, most of these studies were conducted with a small population at a single center. Moreover, there are no prospective studies to confirm the definite superiority of uncut Roux-en-Y anastomosis for patients after distal gastrectomy. Therefore, we propose a multicenter, prospective, randomized clinical trial primarily to elucidate the safety of uncut Roux-en-Y anastomosis compared to Billroth II anastomosis and to innovatively evaluate patients’ nutritional status and quality of life. The SPIRIT 2013 checklist provided the recommended items to address in a clinical trial protocol (shown in Additional file 2).

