Moreover, we plan to do some subgroup analysis using the different preoperative nutrition status or the postoperative pathological stages as analysis factors. In our trial, region supervisors will monitor the researchers with regard to completeness of data collection. However, it is unavoidable to have some missing data. As we mentioned in the “Elimination criteria” section, patients whose efficacy evaluation data for the treatment are incomplete will be excluded. Other missing data are divided into two kinds—important data and common data—depending on the relationship of the missing data and the primary or secondary assessment of the trial. We will record and report the number of cases where the randomized treatment cannot be performed. We will try to fix the common data using statistical tools. However, if the missing data are important, we will employ a specialist of statistics to analyze and decide how to deal with them.

However, bias exists in all clinical trials. In our trial, the blinding of the surgeons and patients as to the intervention is the most challenging aspect of designing a randomized controlled trial involving surgical procedures. For others, the blinding of patients should also be considered to reduce potential bias. Therefore, we set purely objective variables as the primary endpoints, including endoscopy and laboratory tests. Additionally, multicenter trials are associated with biases, including differences in operative skill. We have tried to eliminate these biases by examining the surgical procedure by another hospital and training all surgeons at participating centers in standard procedures.

To conclude, based on previous efforts in the reconstruction of distal gastrectomy, the proposed CSGC002 trial represents a multi-center, prospective, randomized controlled trial to test the hypothesis that uncut Roux-en-Y anastomosis can reduce postoperative complications and improve the nutritional status of gastric cancer patients after D2 gastrectomy compared to Billroth II anastomosis. We believe that the results of the trial will significantly contribute to the evidence on which to base the reconstruction of distal gastrectomy.

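### The trial is sized on one primary outcome, but the protocol lists four unranked primary indices under a single undivided 5% level

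*Protocol article*

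**What the plan says.** The protocol article describes the primary outcome in four places.

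- **Sample size:** the trial is "a superiority trial whose primary outcome is postoperative reflux gastritis or not". The assumption is that "the predicted rate of postoperative reflux gastritis will be 8% for the uncut Roux-en-Y anastomosis group and 12% for the control group" of Billroth II, "with 80% test power and a 5% significance level". One binary outcome is powered.
- **Elimination criteria:** evaluability for the primary outcome (singular) is judged over six time-points: 6 months and 1, 2, 3, 4 and 5 years. Three months is not among them.
- **Abstract (Methods/design) and Outcome measures:** "The primary assessment indices of the study are reflux gastritis, esophagitis, bile regurgitation, and anastomotic ulcer". No order, composite or all-must-succeed rule is given. Outcome measures then lists hemoglobin, albumin, total protein and similar values under nutritional status, which is secondary.
- **Discussion:** "we set purely objective variables as the primary endpoints, including endoscopy and laboratory tests".

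The Statistical analysis section sets one general significance level of 5%, with no division between outcomes and no statement of sidedness.

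**The concern.** The identity of the primary outcome decides what the trial's main result is. Here the powered question (reflux gastritis) and the listed primary question (four indices) differ, and nothing in the article says which governs. The main claim could therefore rest on whichever index turns out favourable, and the stated 5% would then not describe the chance of a false main claim.

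A second ambiguity sits inside reflux gastritis itself. Six time-points are named, but the rule that turns them into one yes/no outcome is not. The outcome could be presence at one visit, presence at the last visit, or any occurrence up to 5 years. The planning rates of 8% and 12% carry no time either, so they cannot be matched to any of these definitions.

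**Working it through.** **1. The plan's own figure.** Inputs from Sample size: 12% v 8%, 80% power, 5% level, 15% drop-out, 1:1 allocation. Per group,

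n = [z_α √(2p̄q̄) + z_β √(p₁q₁ + p₂q₂)]² / (p₁ − p₂)²,

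with √(2 × 0.10 × 0.90) = 0.4243 and √(0.1056 + 0.0736) = 0.4233.

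- Two-sided: (1.960 × 0.4243 + 0.842 × 0.4233)² / 0.0016 gives 882; 882/0.85 gives 1038.
- One-sided (1.645): 695; 695/0.85 gives 818.

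Neither gives the stated 416 per group. That is a separate matter. It is shown because it bears on the cost of the alternative fix in step 4. The error rates below do not use it.

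**2. Four indices, each tested at 5%, any one sufficing.** These two conditions are assumptions; the article states neither.

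- Independent tests: 1 − 0.95⁴ = 1 − 0.8145 = 18.5%, which is 3.7 × 5%.
- Upper bound under any dependence: 4 × 5% = 20%.
- Equally correlated two-sided normal test statistics, c = 1.96: 1 − ∫ [Φ((c − √ρ t)/√(1−ρ)) − Φ((−c − √ρ t)/√(1−ρ))]⁴ φ(t) dt.

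| Assumed correlation | At least one false positive | Multiple of 5% |
|---|---|---|
| 0 | 18.5% | 3.7 |
| 0.3 | 17.4% | 3.5 |
| 0.5 | 15.6% | 3.1 |
| 0.7 | 13.0% | 2.6 |
| 0.9 | 9.4% | 1.9 |

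With one-sided 5% tests the figures are slightly lower (about 16% at 0.3 and 9% at 0.9). With two-sided tests the table counts significance in either direction. Counting only results that favour uncut Roux-en-Y, the independent case is 1 − 0.975⁴ = 9.6% against a nominal 2.5%, a ratio of 3.9.

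**3. Reflux gastritis alone confirmatory.** There is one index, so the number of indices adds nothing to the 5%.

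**4. Keeping four co-equal primaries with Bonferroni.** Each is tested at 5%/4 = 1.25%. The overall rate is 1 − 0.9875⁴ = 4.9% if independent, and at most 5%. The formula in step 1 with z = 2.498 gives 1254 evaluable per group for reflux gastritis, or 1254/0.85 = 1476 after drop-out. Power at 416 per group is Φ[(0.04√416 − 2.498 × 0.4243)/0.4233] = Φ(−0.576) = 28%. With 416 × 0.85 = 354 evaluable it is 23%.

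**The case against.** The strongest reply is that Sample size already settles the matter. It names one outcome, the Elimination criteria use the singular, and the four indices may be no more than the endoscopic findings to be recorded. A rule for multiple outcomes is often left to the analysis plan, which is not shown. The article never says that each index is tested separately or that one success is enough. The Discussion's mention of laboratory tests is a remark about objectivity, not an endpoint definition.

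Much of this stands. The inflation must be stated conditionally, and the absence of a multiplicity rule is not in itself a fault. The remark on laboratory tests is the weakest part of the contradiction. What does not stand is that the conflict can be left to the analysis plan: such a plan can add a testing rule, but it cannot make one primary outcome and four primary outcomes both true.

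A reader might infer three stronger things that the article does not support:

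- **That the false-positive rate is about three times 5%.** This needs a correlation near 0.5, and no correlation is given.
- **That the 3-month endoscopy done only if necessary (Table 1) feeds the primary outcome, or that no visits are attached to it.** The Elimination criteria list six visits and omit 3 months. Only the way they combine is missing.
- **That separate tests at six visits raise the error to 26%.** The sum 1 − 0.95⁶ = 26.5% assumes independence, which is implausible for repeated endoscopies in the same patients, and nothing says that visits are tested separately.

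**Conclusion.** The contradiction is plain in the text and has to be resolved: one primary outcome under Sample size and Elimination criteria, four under the Abstract and Outcome measures, and a looser description in the Discussion. Its effect on the error rate depends on which text governs. It is nil if reflux gastritis alone is confirmatory. It is 18.5% under independence, and about 17% to 9% for correlations of 0.3 to 0.9, if any of the four may carry the claim at 5%. The correlations are assumed, the tests are treated as approximately normal, and Fisher's exact test on a rare index would lower the figures somewhat. The missing rule for combining six time-points is a second, smaller gap in the same definition.

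**What to change.** - In the Abstract, Outcome measures and Discussion, name reflux gastritis as the sole primary outcome, as Sample size already does.
- Define it as one result over the six time-points in the Elimination criteria. Cumulative incidence at the scheduled endoscopies is one example. State that the 8% and 12% refer to that definition.
- Specify a single final confirmatory test. Its level should take account of any efficacy look at this outcome at the 400-case interim analysis, because a full 5% at the end would not hold if superiority could also be declared then.
- List esophagitis, bile regurgitation and anastomotic ulcer as secondary, and remove laboratory tests from the description of the primary endpoints.

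The choice should be made without sight of comparative outcome data, since recruitment has been running since January 2016.

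The change is mainly one of wording; the real cost is that three indices lose primary status. Keeping all four as primary at 1.25% each would be much dearer: 1476 per group after drop-out for reflux gastritis, or 28% power at the planned 416 even with no drop-out. Choosing a single fixed visit, or adjusting the secondary outcomes, would be a matter of preference and is not needed to resolve this point.

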### Elimination criteria

Efficacy evaluation of primary outcome: if data for more than three of a total of six time-points (6 months, 1 year, 2 year, 3 year, 4 year, and 5 year) missed for the patient.Did not evaluate the efficacy according to the predetermined plan.

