### Randomization

After completing an initial assessment and signing an informed consent form, participants will be randomized into two groups: the experimental group undergoing uncut Roux-en-Y anastomosis and the control group undergoing Billroth II anastomosis.

The randomization is undertaken only by the qualified researchers. A secure randomization routine will give each patient an identification number. This number must be recorded in the randomized list together with the randomized data. The completed list should be signed by the investigators and submitted to the data center along with the patients’ initial information. Patients’ identification numbers should be marked in all the relevant reports.

During the randomization, allocation concealment should be maintained. All the patients will be randomized into groups in a 1:1 ratio, and neither surgeons nor patients will be informed as to the randomization arm before surgery. Once D2 gastrectomy has been performed, the randomization arm of the patient will be revealed and the corresponding anastomosis will be performed.

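### The end-of-study analysis is restricted by recurrence status, a post-randomisation event, with no endpoint exempted; this contradicts the planned survival, recurrence and metastasis rates

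*Protocol article*

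**What the plan says.** The Outcome measures section of the protocol article ends with the rule "Only follow-up data of patients without recurrence after 1 year of surgery will be analyzed at the end of the study". It follows the full list of primary and secondary outcomes and is not tied to any of them.

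The same section states:
- on follow-up: "All patients enrolled in this trial will be followed up regularly at stated intervals after the surgery for an average of 5 years";
- on secondary outcomes: "The secondary assessment indices are nutritional status, quality of life, perioperative complications, overall survival rate, and others";
- on oncological rates: "Overall survival rates for 1, 3, and 5 years after the surgery as well as recurrence and metastasis rates will be calculated".

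The Statistical analysis section adds: "For survival analyses, Kaplan-Meier curves and log rank tests will be used". It also plans a Cox model for prognosis.

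On timing, the Randomization section says: "Once D2 gastrectomy has been performed, the randomization arm of the patient will be revealed and the corresponding anastomosis will be performed". Every recurrence therefore comes after randomisation.

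Two other sections also remove randomised patients. Elimination criteria drops those who miss more than three of the six primary-outcome time points (6 months and years 1 to 5). Uniformity in surgical performance rejects cases whose operation falls short of the standard. The article names no all-randomised analysis set that would override the recurrence rule.

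**The concern.** An analysis set should not be defined by something that happens after randomisation, least of all by one of the trial's own outcomes. A recurrence rate cannot be estimated in patients selected for not having recurred. Survival after cancer surgery cannot be estimated as a rate from surgery once patients with the worst prognosis have been removed.

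This is a stated rule, not a detail left to a fuller document. An analyst who followed it literally would report wrong recurrence and survival figures. The reflux and nutrition comparisons would describe a selected group, and endoscopies already performed would go unused.

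**Working it through.** **1. The two readings against the promised endpoints.** The phrase about recurrence after 1 year can be taken in two ways.

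| Reading | Recurrence | Overall survival |
|---|---|---|
| Only patients recurrence-free at 1 year are kept | 0% in year 1 by construction; later recurrence can be estimated, but only conditionally | 1-, 3- and 5-year figures are conditional on 1-year status, not rates from surgery in all randomised patients |
| Only patients with no recurrence later than 1 year are kept | 0% after year 1 by construction | Later survival is inflated, because patients with late recurrence are removed |

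Neither reading gives the rates that the section promises.

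**2. Size of the survival distortion (illustration).** The documents give no survival or recurrence figures, so all inputs here are assumed: true 5-year survival 60%, a fraction r removed for first-year recurrence, and 5-year survival s in those removed. The reported figure is (0.60 − r·s)/(1 − r).
- r = 0.10, s = 0.20: (0.60 − 0.02)/0.90 = 64%
- r = 0.20, s = 0.10: (0.60 − 0.02)/0.80 = 72.5%
- r = 0.30, s = 0.05: (0.60 − 0.015)/0.70 = 84%

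**3. Reflux assessments lost.** Two of the six primary-outcome time points, 6 months and 1 year, fall within the first year, and endoscopy is scheduled at both.
- Under the first reading, a patient who recurs between months 6 and 12 loses a valid 6-month assessment. The 12-month assessment generally does not precede recurrence.
- Under the second reading, both the 6-month and the 12-month assessments precede the recurrence that leads to exclusion.

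**4. Bias between arms (illustration, assumed inputs).** Suppose there is no true effect, with two equal strata whose reflux rates are 6% and 18% (12% overall). If 10% are excluded in every stratum, the observed rate is (0.45 × 0.06 + 0.45 × 0.18)/0.90 = 12.0%. If one arm instead loses 30% of its high-risk stratum, its rate is (0.45 × 0.06 + 0.35 × 0.18)/0.80 = 11.25%, against 12.0% in the other arm. A spurious difference appears only when exclusion differs by arm in relation to reflux risk.

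**5. Sample size.** Inputs from the Sample size section: "8% for the uncut Roux-en-Y anastomosis group and 12% for the control group of Billroth II anastomosis", 5% significance, 80% power, 15% drop-out and 416 per group. Sidedness is not stated.

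The planned figure does not reproduce. With pooled variance, n = [zα√(2·0.10·0.90) + zβ√(0.12·0.88 + 0.08·0.92)]²/0.04². This gives 882 per group two-sided (882/0.85 = 1038 with drop-out) and 695 one-sided (818 with drop-out). That is a separate matter, and this point does not rest on it. It does explain the low starting power below.

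Evaluable n per group is 416 × 0.85 × (1 − r), where r is the share excluded for recurrence beyond drop-out (assumed).

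| r | n per group | Power, two-sided | Power, one-sided |
|---|---|---|---|
| 0 | 354 | 42.6% | 55.1% |
| 0.10 | 318 | 39.0% | 51.5% |
| 0.20 | 283 | 35.4% | 47.6% |

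The row r = 0 is the case where every recurrence already falls within the 15% drop-out. Over this range the rule costs 0 to 42.6 − 35.4 = 7.2 points of two-sided power.

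**The case against.** The strongest defence is that the sentence was meant only for functional and nutritional follow-up, where recurrent cancer obscures the effect of the reconstruction. Since the article also plans survival curves and recurrence rates, its authors can hardly have meant to remove recurrences from those. This is plausible, but the text does not say so. Even on that reading, usable assessments made before recurrence are discarded.

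Three stronger conclusions are tempting, and the objection to each stands.
- *A reader might infer that the survival and recurrence endpoints become meaningless.* That is literally true only of the recurrence rate in the excluded window. Under the 1-year reading, later recurrence and 3- and 5-year survival can still be computed, as conditional figures.
- *A reader might infer that the reflux comparison is biased.* No document shows that recurrence or its detection differs by arm, and the arm is revealed only after the resection. With equal recurrence, the illustration shows no spurious difference.
- *A reader might infer a definite loss of power.* The article gives no recurrence rate and does not define drop-out, so the overlap is unknown. The missing-visit rule would also remove some of the same patients: one seen only at 6 months and 1 year misses four of six time points and is eliminated anyway. The low starting power belongs to the sample-size calculation, not to this rule.

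**Conclusion.** The point holds and should be corrected before the final analysis. As written, the rule selects patients on a post-randomisation outcome, exempts nothing, and contradicts the survival, recurrence and metastasis rates and the survival analyses in the same article. That conclusion rests on the text alone.

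For survival and recurrence, the figures would be wrong on either literal reading: zero recurrence by construction in one window, and survival that is conditional or inflated. How far survival would be off depends wholly on assumed inputs. For reflux and nutrition, the certain effects are a changed population and lost information; bias between arms is a risk, not a demonstrated fault. The further loss of evaluable patients runs from none to 20%, or about 0 to 7 points of two-sided power. This rests on an assumed recurrence rate of 10–20% at the upper end, unknown overlap with drop-out, and a two-sided test that the article does not specify.

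**What to change.** 1. Remove the sentence as the general analysis-set rule.
2. Analyse overall survival, recurrence and metastasis in all randomised patients.
3. Analyse reflux and nutrition outcomes in all randomised patients, using scheduled assessments up to recurrence or death, and state how those events are handled (for example as intercurrent or competing events).
4. Keep the recurrence-free set as a labelled sensitivity analysis, and state exactly which recurrence window defines it.
5. Align the exclusions under Elimination criteria and Uniformity in surgical performance with this set; otherwise they would still remove randomised patients.

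At a minimum, limiting the rule's scope and exempting survival, recurrence and metastasis would remove the contradiction, but it would leave the loss of pre-recurrence assessments. The cost is protocol and analysis-plan wording and slightly more analysis. All enrolled patients are already to be followed, so no new data are needed.
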